## Materials and methods

### Study design

This is a prospective, randomized, controlled clinical trial in a multi-hospital health care system among patients with high levels of anxiety with an indication for primary total hip or knee arthroplasty. We will be comparing two groups: one that receives access to RxWell™ and usual care and one that only receives the usual care. Figure 1 and Table 1 show the study design, timing of pre- and postoperative use of RxWell™, and follow-up evaluations. CONSORT 2010 items and CONSORT-SPI 2018 checklist are presented for the abstract (Table 2) and main text (Table 3). The SPIRIT Checklist is presented as an additional file (Additional file 1). We will recruit patients from 4 hospitals within the *UPMC system* (*UPMC Shadyside*, *Magee*, *East*, and *Passavant hospitals*). In this pilot, randomized feasibility trial, we will prospectively allocate 34 subjects in the control group, and using a 1:3 allocation, we will have 102 in the intervention group (two-sided *t*-test with alpha of .05, power of .8, with a 3:1 ratio and a 50% drop out rate for a Cohen’s *d* of .8). A block randomization schedule generated using the R software (version 4.2.1, R Core Team, 2022) will be used to allocate the participants to either dCBI plus usual care (*intervention*) or usual care (*control*) with a 3:1 allocation (Table 2). Investigators will be blinded for group assignment in REDCap, and they will also be blinded for the monthly reports. Research coordinators, the statistical data analysts, and subjects will not be blinded. To make sure investigators are blinded to the intervention, investigators will not have access to the randomization table and surveys in REDCap. Investigators will only be able to access the eligibility checklist and informed consent surveys in REDCap. Patients will be randomized immediately after the PROMIS Anxiety 4a and the PROMIS Depression 4a patient assessment by a research coordinator using REDCap. We do not anticipate any requirement for unblinding, but if required, the director of clinical research operations, regulatory specialist, study coordinators, or the principal investigator will have access to group allocations and any unblinding will be reported.

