### Outcome measures

We will assess the following:RxWell™’s acceptance by practitioners and patients will be measured by qualitative interviews among all practitioners and randomly selected patients.Workflow changes brought on by the implementation of RxWell™, andImpact of RxWell™, on mood disorders (anxiety, depression, pain catastrophizing) in the immediate pre- and post-operative periods.

We will also test the impact of RxWell™, onSleep disordersFatigueAbility to participate in social rolesPain interferenceCognitive functionPerioperative painOpioid requirements and opioid morphine equivalents,Functional recovery, andResource utilization associated with the surgery and recovery (hospital length of stay, duration of physical therapy).

Ultimately, our outcome is to determine if RxWell™ can improve surgical outcomes.

Primary and secondary outcomes will be measured at baseline preoperatively, on the day of the surgery, and 1, 2, and 3 months after surgery (Table 1). Preoperative data will be collected virtually via REDCap surveys by study team members. Postoperative data collection will be performed via email surveys and telephone calls by a member of the study team. Research coordinators collecting outcomes will not be blinded to group assignment. Patients will not be blinded and will be informed that the study aims to assess the effect of dCBI in addition to usual care compared to usual care alone on surgical patients.

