#### Long-term follow-up

Both groups will be assessed at 1, 2, and 3 months after the surgery, which corresponds to 2, 3, and 4 months after the enrollment. Participants from both groups will have to complete the same instruments described above and the post-surgical survey created in REDCap, which records potential post-surgical complications and additional measures like the length of stay in the hospital, the time to ambulation, and the use of physiotherapy. In addition, participants will also have to complete a satisfaction survey about RxWell™ at the 3-month timepoint, corresponding to the last interaction with the participants. The purpose of this follow-up is to collect data on long-term effects of the interventions and document any changes that might take place in the participant’s disease condition, their frequency of CBI intervention practice, and other additional changes noted.

Users will complete GAD-7and PHQ-8 bi-weekly to monitor their behavioral health over time, and the digital behavioral health coaches will review the scores, free text in each technique, and user message to the coach within two business days. In the event of a risk escalation, coaches will contact the coach supervisor to notify a high-risk situation or an interaction with a user where they encounter concerning symptoms that may be exhibited either within the context of a message sent to the coach or free text within a technique.

As for behavioral studies, trials are commonly designed with a waitlist control group. This approach would allow that all participants have an opportunity to utilize the intervention; however, in the current trial with a focus on feasibility, we will use the randomized approach and plan the waitlisted approach for a larger clinical trial.

The data entry and coding will be performed by study coordinators electronically using the REDCap. All the data are secured behind a firewall within the University of Pittsburgh (Clinical and Translational Science Institute at the University of Pittsburgh Grant Number UL1-TR-001857).

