### Data analysis

The primary hypotheses and all other comparisons will be assessed with intention to treat estimates. Between-group differences in primary outcomes, PROMIS anxiety and depression scores, PHQ-8, and GAD-7 scores will be tested using independent two sample *t*-tests on the day of the surgery. Two-sided tests using *p* values of < 0.05 will be considered statistically significant. Differences of tests showing Cohen’s *D* of > = 0.8 will be considered clinically significant. Participants with missing primary timepoint data will be excluded from testing. For secondary outcomes, we will calculate descriptive statistics i.e., usage of RxWell™, adherence, use frequency, etc. Testing of treatment and control group differences in secondary outcomes will be applied to appropriate variables, i.e., participant perioperative pain, opioid equivalent requirement, functional recovery, etc., for time point baseline, day of surgery, and 1 month follow-up. Continuous variables will be described using means and standard deviations. Categorical variables will be described using frequencies/proportions. We will use independent sample *t*-tests and chi-squared analyses to examine between group differences. Fisher’s exact tests and Mann-Whitney *U* tests will be performed in replacement of their counterpart parametric tests where appropriate. Missing data will be removed from denominators, proportions, distributions, and testing of their differences. We will use longitudinal mixed effect models to account for within person variance across all time points as a secondary analysis.

Baseline patient demographics, comorbidities, and procedure details will be stratified by group, and described standardized mean differences will be calculated to compare groups (Table 1). As a secondary analysis, we will use longitudinal mixed effect models to account for within person variance across all time points. We will adjust models using demographics found to have greater than 0.2 standardized mean difference. No subgroup analysis will take place.

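### The simple between-group tests of secondary outcomes include baseline and leave out months 2 and 3, and the mixed models that span those months are not tied to an arm comparison there

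*Protocol article*

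**What the plan says.** Data analysis gives the rule for secondary outcomes in one sentence. It opens "Testing of treatment and control group differences in secondary outcomes will be applied to appropriate variables", gives pain, opioid requirement and functional recovery as examples, and ends by fixing the times: "for time point baseline, day of surgery, and 1 month follow-up". The method follows: "We will use independent sample *t*-tests and chi-squared analyses to examine between group differences", with non-parametric or exact substitutes where needed.

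The collection schedule is longer. Outcome measures states: "Primary and secondary outcomes will be measured at baseline preoperatively, on the day of the surgery, and 1, 2, and 3 months after surgery". Long-term follow-up repeats the later visits for both arms, "Both groups will be assessed at 1, 2, and 3 months after the surgery", and gives the reason: "The purpose of this follow-up is to collect data on long-term effects of the interventions". The abstract gives the intervention arm access to the app until 3 months after surgery.

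Data analysis also plans a second layer: "We will use longitudinal mixed effect models to account for within person variance across all time points as a secondary analysis". Its next paragraph repeats this and adds that the models will be adjusted for demographics whose standardised mean difference exceeds 0.2. It does not say which outcomes are modelled, and it names no arm effect at any visit.

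**The concern.** The hypotheses at the end of the Background are about recovery after surgery: pain and opioid need, function, complications and resource use. The abstract's discussion goes further and points to chronic postsurgical pain. For such questions the later visits matter at least as much as the early ones. Yet the list of test times stops at month 1 and uses one of its three places on baseline, where a comparison of arms does not estimate the effect of the intervention.

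The risk is to interpretation. If the simple tests are followed as written, the report will carry baseline p-values that answer no trial question, and no simple comparison at months 2 and 3. If a late comparison is then wanted from the mixed model, its form would have to be chosen without guidance from this text, possibly after results are known.

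**Working it through.** **1. The plan's own figure, and whether this point touches it.** Inputs from Study design and Sample size calculation: two-sided alpha 0.05, power 0.80, Cohen's d 0.8, ratio 3:1, 50% retention.

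- Control n before dropout, normal approximation: (1 + 1/3) × (1.960 + 0.842)² / 0.8² = 1.333 × 7.85 / 0.64 = 16.4, rounded up to 17. The noncentral t gives 16.85, also 17.
- Intervention n: 3 × 17 = 51. Power with 17 and 51 is 0.804.
- Allowing for 50% retention: 17 / 0.5 = 34 and 51 / 0.5 = 102, total 136.

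The stated 136 is reproduced. It rests on the day-of-surgery primary comparison alone, so changing the times of the secondary tests does not alter it.

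**2. Collection schedule against test times.** In Table 1, five secondary rows are marked at all five times: the PROMIS 29+2 domains, pain catastrophizing, pain scores, analgesic consumption and HOOS/KOOS.

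| Time | Collected in both arms | Simple between-group test | Within the mixed models' span |
|---|---|---|---|
| Baseline | yes | yes | yes |
| Day of surgery | yes | yes | yes |
| Month 1 | yes | yes | yes |
| Month 2 | yes | no | yes, no arm contrast named |
| Month 3 | yes | no | yes, no arm contrast named |

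So 1 of 3 test times is baseline, 2 of 4 visits after baseline have no simple test, and 2 of the 3 visits after the day of surgery have none. The article gives no reason for stopping at month 1.

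**3. Is baseline a useful test time?** If the baseline forms come before allocation, any difference between randomised arms is due to chance, and a test of it says nothing about the app. If some come after allocation, a difference is still not the effect the trial wants to measure. The plan already describes baseline demographics, comorbidities and procedure details by standardised mean differences, so it has a suitable descriptive tool.

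**4. What do the mixed models supply?** They span every time point, so months 2 and 3 enter the analysis. The purpose given for them is to account for variation within a person. That describes how repeated measurements are handled. It does not state which comparison of arms will be reported.

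**The case against.** The strongest reply is that this is a two-tier plan: simple tests at the early times and a longitudinal model over all visits. The models are to be adjusted for demographics that differ between arms, which makes little sense unless the arms are being compared. Fixed effects and visit contrasts are also commonly left to an analysis plan, which is not shown here.

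Much of this stands. A reader might infer that months 2 and 3 never enter a comparison of the arms. The documents do not support that, because the models cover those visits and probably do contain an arm term. The missing model terms alone would not be a finding. What remains is what the article itself fixes: a list of test times that contains an uninformative one and stops short of the follow-up the trial sets up to study long-term effects.

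Other tempting readings also go too far:

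- **No treatment effect is possible at baseline.** This is evidently intended but not secured. Study design says "Patients will be randomized immediately after the PROMIS Anxiety 4a and the PROMIS Depression 4a patient assessment", Table 1 puts baseline 3–4 weeks before surgery, and the abstract starts app access 1 month before surgery. Some baseline forms could therefore follow allocation.
- **Months 2 and 3 are the whole long-term follow-up.** Month 1 stands under that heading too.
- **The test times do not fit complications and satisfaction.** The tests are limited to suitable variables, and neither outcome is among the examples. The satisfaction survey is about the app, so no arm comparison is implied.
- **The baseline tests carry a quantifiable error rate.** If independence is assumed, the chance of at least one false positive is 1 − 0.95³ = 14% for the three outcomes named in Data analysis, and 1 − 0.95⁹ = 37% for the nine listed under Secondary outcomes. The count is arbitrary, the outcomes are probably correlated, and no decision in the plan depends on a baseline p-value. This is not a measure of harm to the trial's conclusions.

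**Conclusion.** The point holds in limited form. The simple secondary tests are placed at one time that cannot inform efficacy, and they omit two of the four visits after baseline. The models that could fill the gap are not linked in the text to an arm comparison at those visits. Data analysis should be reconciled with Outcome measures and Long-term follow-up.

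The consequence is confined to secondary outcomes measured repeatedly. The primary day-of-surgery tests and the sample size of 136 do not change, and no bias in a trial conclusion is shown. The conclusion assumes that the sentence on test times means what it says and that no fuller document replaces it. It is worth correcting because these outcomes carry the postoperative hypotheses and the data are already to be collected.

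**What to change.** In Data analysis:

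1. Remove baseline from the times at which secondary outcomes are tested. Describe baseline values of these outcomes by arm, using the standardised mean differences already planned for baseline characteristics.
2. For each repeatedly measured secondary outcome, state that the arm difference, with its confidence interval, will be estimated on the day of surgery and at 1, 2 and 3 months from the planned mixed model, with arm, visit, arm-by-visit interaction and baseline value as terms.
3. State that the baseline forms used for adjustment are completed before allocation is known and the app is opened. If that cannot be ensured, say so, because the baseline value would then not be a clean covariate.
4. Label these secondary estimates exploratory.

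The cost is small. Each such outcome goes from three comparison times (one of them baseline) to four post-baseline estimates. No further visits, data or participants are needed.

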Telemedicine represents increasingly common strategies for patient care. Similarly, digital Cognitive Behavioral Intervention (dCBI) could be an effective strategy for overcoming some of these barriers. There is preliminary data suggesting that dCBI could be an effective treatment for depression and anxiety in primary care [30]. However, the implementation of dCBI for reducing perioperative psychological and psychosomatic conditions is limited. RxWell™ is an app that includes evidence-based cognitive behavioral techniques and can be used remotely to teach coping strategies based on CBI. It has proven to successfully help patients with inflammatory bowel disease [31].

We are using the RxWell™ dCBI in this clinical trial among orthopedic patients and named the trial as SuRxgWell. In this SuRxgWell trial, we hypothesize that the use of RxWell™ will reduce the deleterious impact of established mood disorders on recovery following primary total hip and total knee replacements by improving the following postoperative outcomes:Pain and opioid requirement,Improved functional recovery,Decrease complications, andReduce resource utilization such as hospital length of stay, postoperative need for visits, and the use of rehabilitation.

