#### Secondary outcomes

Pain catastrophizingSleep disordersFatigueAbility to participate in social rolesPain interferencePerioperative pain at rest and during movementOpioid requirements and opioid morphine equivalents,Functional recovery, andResource utilization associated with surgery and recovery (hospital length of stay, duration of physical therapy). We will adjust for surgical decision during the resource utilization modeling as surgeons vary in their decision algorithms for patient discharge timing.

In addition, as part of secondary outcomes, we will record participants’ usage of RxWell, adherence, use frequency, number of techniques completed, and the path in the RxWell platform (anxiety vs. depression) the patient is utilizing. Participants will also complete a satisfaction survey at the end of their participation. The instruments and specific timepoints at which these outcomes are measured are collected in Table 1. The study team will receive monthly reports providing the number of techniques completed, the number of messages to the coach, and the program used in *RxWell* (anxiety vs. depression).

The tools used are as follows:Pain catastrophizing—Pain Catastrophizing Scale [34]Sleep disorders—PROMIS 29+2 [35]Fatigue—PROMIS 29+2 [35]Ability to participate in social roles—PROMIS 29+2 [35]Pain Interference—PROMIS 29+2 [35]Perioperative pain at rest and during movement—pain medications [36]

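### Duration of physical therapy is right-censored at the last survey, but the stated rule removes missing values with no exception; if an unobserved end date counts as missing, the arm comparison is biased, in a direction that depends on the effect

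*Protocol article*

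**What the plan says.** All places are in the Protocol article.

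- **Outcome.** Outcome measures and Secondary outcomes both list resource utilization and name two components: hospital length of stay and duration of physical therapy. Background includes resource utilization among the hypothesised improvements, in terms of "postoperative need for visits, and the use of rehabilitation".
- **Observation.** Under Long-term follow-up, a post-surgical survey at 1, 2 and 3 months records, among other things, the use of physiotherapy. Month 3 is described as "corresponding to the last interaction with the participants".
- **Tests.** Data analysis describes continuous variables by means and standard deviations and says "We will use independent sample *t*-tests and chi-squared analyses to examine between group differences". It adds that "Fisher’s exact tests and Mann-Whitney *U* tests will be performed in replacement of their counterpart parametric tests where appropriate".
- **Missing data.** The same section says "Missing data will be removed from denominators, proportions, distributions, and testing of their differences". No outcome is exempted.
- **Modeling.** Secondary outcomes says "We will adjust for surgical decision during the resource utilization modeling as surgeons vary in their decision algorithms for patient discharge timing". The type of model is not stated, and neither censoring nor ongoing therapy is mentioned.

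**The concern.** Total duration of therapy is known only once therapy has ended. For a patient still attending at the last completed survey, the data say only that the duration exceeds the time observed. The value is unobserved because it is long, so it cannot be treated like a skipped questionnaire item.

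Three hypothetical patients show this. One ends therapy at week 7 and scores 7. One is still in therapy at week 13 and has no end date. One is still in therapy at the month-1 survey and is then lost. Under a removal rule the second and third drop out of the comparison, which selects on the outcome after randomisation. That sits badly with the intention-to-treat estimates which Data analysis promises for all comparisons. A rank test does not help, since removed patients have no rank.

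At stake is one of the resource-use results of a pilot meant to inform a later trial. A distorted estimate would mislead its planning.

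**Working it through.** **1. The plan's own figure.** The article gives no figure for therapy duration. Its only related figure is the sample size. With d = 0.8, two-sided alpha 0.05, power 0.80 and a 3:1 ratio, the normal formula gives controls = (1 + 1/3)(1.960 + 0.842)² / 0.8² = 16.35, so 17. The noncentral t gives 16.85, also 17. Then 17 + 51 = 68, and 68 / 0.5 = 136. The stated 136 reproduces and does not depend on this point.

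**2. Assumptions.** All are mine, since the documents give no duration, spread or share still in therapy: lognormal durations, a cut-off H of 13 weeks, control median m of 6 to 12 weeks, log-SD s of 0.5 or 0.7, intervention durations 20% shorter, and everyone followed to month 3.

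**3. Formulas.** With z = (ln H − ln m)/s:
- full mean M = m·exp(s²/2)
- share still in therapy = 1 − Φ(z)
- mean after removal = M·Φ(z − s)/Φ(z)
- mean within 3 months (capped at H) = M·Φ(z − s) + H·(1 − Φ(z))

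**4. Worked case, m = 8 and s = 0.7.**
- Control: z = 0.694, M = 10.22, 24% still in therapy, mean after removal 6.73, mean within 3 months 8.26.
- Intervention (m = 6.4): z = 1.012, M = 8.18, 16% still in therapy, mean after removal 6.03, mean within 3 months 7.11.

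Differences in weeks, from unrounded means:

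| Control median, log-SD | Full duration | After removal | Within 3 months |
|---|---|---|---|
| 8, 0.5 | 1.81 | 0.95 (52%) | 1.36 (75%) |
| 8, 0.7 | 2.04 | 0.70 (34%) | 1.14 (56%) |

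Over medians of 6 to 12 weeks, removal keeps 72% down to 19% of the full difference and capping keeps 89% down to 33%. Removal is also wrong against the 3-month quantity: 0.95/1.36 = 70% and 0.70/1.14 = 61%.

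**5. Direction under other effect shapes (also assumed).**
- *Effect only in patients who finish early.* In each arm a share q stays about 16 weeks; the others average 8 weeks in controls and 6 under intervention. The full difference is 2(1 − q). After removal it is 2. For q = 10%, 20% and 30% the ratio 1/(1 − q) is 111%, 125% and 143%: inflated. Capping keeps 100%.
- *Long stayers shortened to just under 3 months.* In controls 20% stay 16 weeks and 80% stay 6, so the mean is 8.0. Under intervention 10% stay 16, 10% stay 11 and 80% stay 6, so the mean is 7.5. Intervention is 0.5 weeks shorter. After removal controls average 6.0 and intervention (0.10 × 11 + 0.80 × 6)/0.90 = 6.56, so intervention appears 0.56 weeks longer: the sign is reversed. Capping at 13 gives 7.4 against 7.2, a difference of 0.2 (40%) in the right direction.

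**6. No effect.** In a simulation with 17 and 51 patients and 20% still in therapy in both arms, rejection rates were 5.8% (capped t-test), 5.4% (t-test after removal) and 5.7% (Mann-Whitney on capped values). The problem is the estimate when there is an effect, not the type I error.

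**The case against.** Several points on the other side stand.

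- **The removal is inferred.** The rule concerns missing data. A patient who reports ongoing therapy at month 3 has answered the survey, and nothing says that this answer is coded as missing. The point is therefore conditional.
- **The t-test is not fixed for this outcome.** Mann-Whitney is allowed where appropriate, and adjusted resource-utilization modeling is foreseen. Neither, as described, says what to do with an unended duration. Ranks would largely work if ongoing cases were kept and tied at the top, but no such rule is stated.
- **Capping is not a bias in itself.** For patients followed to month 3, capping gives the mean therapy time within 3 months, a legitimate quantity. Only an earlier last-survey time, entered for a patient lost while in therapy, understates it.
- **Coding detail is usually left to an analysis plan.** True. But the article itself states a removal rule without exception, and that rule does not suit this outcome.

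A reader might infer three stronger things, which the documents do not support. The first is that the difference is always pulled toward zero; that needs roughly proportional shortening. The second is that the planned 50% loss makes most last surveys fall before month 3. The sample size section gives 50% retention alongside the day-of-surgery comparison, and no rate of loss between months 1 and 3 is given. The third is that this outcome will be tested at month 1, because secondary tests are set "for time point baseline, day of surgery, and 1 month follow-up". The examples in that open-ended list do not name physical therapy. Under the assumptions above 68% to 98% of controls would still be in therapy at about 4.35 weeks, but nothing shows how many patients this would concern.

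**Conclusion.** The point holds in conditional form. The article names a duration that is right-censored at the last survey, states a removal rule without exception, and says nothing on censoring where it mentions modeling. If an unobserved end date is treated as missing, the longest durations are removed selectively and the comparison is biased. Under proportional shortening with an assumed control median of 8 weeks, about 34% to 52% of the true difference is kept; under other shapes the result is inflated or reversed. The actual size is unknown, because it depends on durations, a share still in therapy and a rate of loss after month 1 that the documents do not give.

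This affects one secondary outcome of a pilot and has low priority.

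**What to change.** In Secondary outcomes and Data analysis:

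1. Define the outcome as physical-therapy time within 3 months of surgery.
2. Record at each post-surgical survey the end date of therapy or that the patient is still in therapy.
3. Exempt this outcome from the missing-data removal rule, and count a patient still in therapy as censored at the last completed survey.
4. Compare arms by the Kaplan-Meier restricted mean to 3 months, or by log-rank or Cox, with the surgical-decision adjustment already foreseen. State the assumption that loss while in therapy is unrelated to the remaining duration.

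The cost is a few sentences, one survey item at visits that already take place, and a standard survival routine. The survey item should be settled before data collection ends, since an end date that was not recorded may not be recoverable. The small downside is that the result applies only to the first 3 months.

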#### Sample size calculation

This is a pilot study meant to inform a subsequent RCT based on this treatment. We will determine if the study is a success if this effect size is observed in our primary outcomes and thus our study is powered based on these effects. From observed estimates in concurrent studies, we expect a clinically significant effect size of Cohen’s D greater than or equal to 0.8. Our primary analysis is comparing PROMIS T scores, GAD-7 and PHQ-8 between groups on day of surgery. Therefore, with 95% confidence, 80% power, using two sided tests and assuming a 50% retention rate, our desired sample size is 136. We will utilize 1:3 allocation, randomizing 34 to the control group and 102 to the intervention group. We are allocating 1:3 to get more accurate estimates around within treatment group improvements as well as to increase the number of patients we can potentially aid by supplying them with the low-risk treatment. The 1:3 allocation was chosen based on the study design and the nature of the intervention. This is a proof-of-concept study in which we want to evaluate the feasibility of RxWell™. In addition, our target subjects are patients with a moderate level of anxiety and/or depression, and we consider it is more ethical to offer a treatment to as many subjects as possible. Sample size calculations were conducted using the Power Analysis and Sample Size Software (PASS - 2022). NCSS, LLC. Kaysville, Utah, USA.

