#### Other variables of interest

At baseline, participants will also complete a demographic, lifestyle, and diagnostic survey, consisting of age, gender, ethnicity, race, height, weight, smoking and alcohol use, medical history, ongoing treatments, and comorbidities.

The following medical data will be gathered: type of operation, surgical indication, and American Society of Anesthesiologists (ASA) classification and if the patient received a nerve block before the surgery.

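### In the secondary mixed models, covariates are chosen by a baseline standardized mean difference above 0.2, a threshold that chance alone crosses for about 31% to 48% of variables

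*Protocol article*

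**What the plan says.** The Data analysis section of the protocol article gives two layers of analysis. The primary outcomes "will be tested using independent two sample *t*-tests on the day of the surgery", with no covariates. The longitudinal models come second: "As a secondary analysis, we will use longitudinal mixed effect models to account for within person variance across all time points". The next sentence sets the covariate rule: "We will adjust models using demographics found to have greater than 0.2 standardized mean difference".

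The set of variables compared between arms is wider than the set that may enter a model. "Baseline patient demographics, comorbidities, and procedure details will be stratified by group", and SMDs are calculated for all of these, but the adjustment sentence admits demographics only. Other variables of interest describes the baseline survey as "consisting of age, gender, ethnicity, race, height, weight, smoking and alcohol use, medical history, ongoing treatments, and comorbidities". The same section lists type of operation among the medical data. Study design names four recruiting hospitals.

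The only other adjustment in the article is for surgical decision in the resource-utilization models (Secondary outcomes).

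**The concern.** Among all randomised participants, a baseline difference between arms is due to chance. Its size says nothing about whether the variable predicts anxiety, depression, pain or function. A rule that selects on imbalance therefore picks a largely random subset of the candidates. It adds variables that may not matter and leaves out any that matter but happen to be balanced.

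The threshold makes this worse. In large samples an SMD of 0.2 is rare by chance; here it is ordinary. The mixed models are also the only planned analysis that uses every time point, and Sample size calculation says the pilot is to inform a later trial. Their estimates and variances are more useful if they come from a model known in advance.

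**Working it through.** **Inputs.** Sample size calculation gives the arms: "We will utilize 1:3 allocation, randomizing 34 to the control group and 102 to the intervention group". It also gives the retention: "with 95% confidence, 80% power, using two sided tests and assuming a 50% retention rate, our desired sample size is 136". The effect size is stated there as "we expect a clinically significant effect size of Cohen’s D greater than or equal to 0.8". The threshold of 0.2 is in Data analysis.

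**1. The plan's own figure.** With d = 0.8, two-sided alpha 0.05, 80% power and 3:1 allocation:

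- Control n = (1 + 1/3) × (1.960 + 0.842)² / 0.8² = 16.4, rounded up to 17, so 17 and 51.
- Dividing by 0.5 for retention gives 34 and 102, total 136. This reproduces the stated number. Exact noncentral-t power at 17/51 is 80.4%.

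**2. Chance of crossing 0.2.** Under randomisation the SMD is approximately normal with mean 0 and SE = √(1/n₁ + 1/n₂), so P(|SMD| > 0.2) = 2 × [1 − Φ(0.2/SE)].

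| Set used for the SMDs | SE | 0.2/SE | P by chance |
|---|---|---|---|
| 34 and 102 (all randomised) | 0.198 | 1.01 | 31.3% |
| 17 and 51 (50% retained) | 0.280 | 0.71 | 47.5% |

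The t distribution gives 31.4% and 47.8%. Simulation gives 31.5% and 47.7% for continuous variables, and about 30–33% and 47–54% for binary variables with prevalence 10% to 60%.

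**3. How many enter by chance.** The article does not say how many items count as demographics. Age, gender, ethnicity, race, height, weight, smoking and alcohol make eight; without the two lifestyle items there are six.

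- Eight: 8 × 0.313 = 2.5 and 8 × 0.475 = 3.8.
- Six: 6 × 0.313 = 1.9 and 6 × 0.475 = 2.9.

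Expected counts add, so they do not depend on the items being independent.

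**4. Effect on error rates and standard errors.** The rule was simulated with eight independent normal candidates, one time point, a linear model, no treatment effect and 20,000 replicates.

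| Variance explained by the candidates | Type I error, 34/102 | Type I error, 17/51 |
|---|---|---|
| 0% | 5.0% | 5.0% |
| 10% | 4.5% | 4.6% |
| 30% | 3.3% | 3.6% |

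There is no inflation. At 30% the model standard error is about 7% too large at 17/51. With irrelevant candidates the mean standard error rises from 0.198 to 0.202 (about 2%) at 34/102, and from 0.280 to 0.295 (about 5%) at 17/51.

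**5. What a prognostic covariate would give.** A covariate that explains a share R² of the outcome variance multiplies the standard error by √(1 − R²). The article gives no R², so a range is assumed.

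- R² = 10%: factor 0.949, so 0.198 becomes 0.188.
- R² = 30%: factor 0.837, so 0.198 becomes 0.166.

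In the single-time-point simulation at 34/102, with a baseline score explaining 30%, a fixed set containing that score brings the true standard error from about 0.205 under the imbalance rule to 0.168.

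**The case against.** The strongest reply is that little is at stake. The rule governs a secondary analysis in a pilot, and success is judged on the primary outcomes. The trigger and the class of candidates are stated in advance, and the rule looks at baseline data and allocation, never at outcomes, so it cannot be used to search for a favourable result. The degrees-of-freedom cost is 2% to 5% of a standard error. The 17/51 case is a worst case, because a mixed model keeps participants with partial follow-up. All of this stands.

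Four stronger readings are tempting, and the article does not support them.

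- **The primary result is compromised.** It is not: those t-tests carry no covariates.
- **The data-driven choice produces false positives.** The simulation shows nominal or conservative error rates.
- **The baseline score never enters.** The models run over all time points and the outcomes are measured at baseline, so baseline may already be a repeated response. It is only not named as a covariate.
- **Known prognostic factors are omitted.** The article does not establish operation type or hospital as predictors of mood scores. Age and gender can enter if they happen to be imbalanced.

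It may also be said that an analysis plan not shown could list the covariates. But the article does not leave the choice open: it states a rule, and a fixed list would replace that rule. Finally, imbalance among those retained could reflect differential dropout and not chance. A threshold that chance crosses 47.5% of the time cannot tell the two apart.

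**Conclusion.** The point holds for the secondary mixed models only. An SMD of 0.2 is 1.01 standard errors at 34/102 and 0.71 at 17/51, so about 31% to 48% of candidate variables qualify by chance. The lower figure applies if SMDs use all randomised, the higher if they use the half expected to remain. Two to four chance covariates are to be expected from six to eight candidates.

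The consequence is a model that cannot be known in advance and that forgoes precision, not a biased or anti-conservative one. The forgone precision depends on how prognostic the fixed covariates are: roughly 5% of the standard error at R² = 10% and 16% at R² = 30%, before small degrees-of-freedom costs. These sizes come from a single-time-point approximation. They would shrink if baseline is already modelled as a repeated response. They may also be smaller for the PROMIS scores, because eligibility (T-score at least 60, not above 70) restricts the baseline range of the qualifying scale.

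**What to change.** Replace the adjustment sentence with a fixed list that applies to every longitudinal mixed model, chosen on prognostic grounds and stated before data are seen:

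- the baseline value of the outcome, as a covariate, or as a baseline response constrained equal across arms if baseline is modelled as a repeated measure;
- operation type (hip or knee);
- hospital;
- age and sex.

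Keep the SMDs in the baseline table as description, with no role in model choice.

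Baseline scores, operation type, age and gender are already collected, and hospital is known from the recruiting site, so no new data are needed. The list uses seven coefficients (one each for baseline, operation, age and sex; three for four hospitals). If all seven were irrelevant, the expected variance factor in a single-time-point model would be 1 + p/(N − p − 3). With p = 7 that is 1 + 7/126 = 1.056 at N = 136 (standard error up 2.7%) and 1 + 7/58 = 1.121 at N = 68 (up 5.9%). This is close to the 2% and 5% that the present rule already costs when its candidates are irrelevant.
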